## Abstract

**Background:**

There is a need for evidence on the most effective and cost-effective approaches for promoting healthy eating among groups that do not meet dietary recommendations for good health, such as those with low incomes or experiencing socioeconomic disadvantage. This paper describes the ShopSmart 4 Health study, a randomised controlled trial conducted by Deakin University, Coles Supermarkets and the Heart Foundation, to investigate the effectiveness and cost-effectiveness of a skill-building intervention for promoting increased purchasing and consumption of fruits and vegetables amongst women of low socioeconomic position (SEP).

**Methods/design:**

ShopSmart 4 Health employed a randomised controlled trial design. Women aged 18–60 years, holding a Coles store loyalty card, who shopped at Coles stores within socioeconomically disadvantaged neighbourhoods and met low-income eligibility criteria were invited to participate. Consenting women completed a baseline survey assessing food shopping and eating habits and food-related behaviours and attitudes. On receipt of their completed survey, women were randomised to either a skill-building intervention or a wait-list control condition. Intervention effects will be evaluated via self-completion surveys and using supermarket transaction sales data, collected at pre- and post-intervention and 6-month follow-up. An economic evaluation from a societal perspective using a cost-consequences approach will compare the costs and outcomes between intervention and control groups. Process evaluation will be undertaken to identify perceived value and effects of intervention components.

**Discussion:**

This study will provide data to address the currently limited evidence base regarding the effectiveness and cost-effectiveness of skill-building intervention strategies aimed at increasing fruit and vegetable consumption among socioeconomically disadvantaged women, a target group at high risk of poor diets.

**Trial registration:**

Current Controlled Trials ISRCTN48771770

## Background

Many Australians do not consume adequate quantities of foods that are important for leading healthy lives. For instance, more than 90% of Australian adults do not eat enough vegetables, and more than 48% do not eat enough fruit for good health
[1]. Compared with those of high socioeconomic position (SEP), individuals of low SEP (e.g., with low levels of education, low incomes, or living in socioeconomically disadvantaged neighbourhoods) are less likely to consume amounts of fruits and vegetables
[2,3]. This puts people of low SEP at increased risk of a range of serious health conditions including obesity, heart disease and stroke, and certain cancers
[4].

Currently little is known about how best to promote fruit and vegetable consumption amongst persons of low SEP. Observational studies of the determinants of unhealthy eating have suggested a number of barriers to healthy eating amongst individuals of low SEP, including relatively lower levels of nutrition knowledge, lack of meal planning/preparation/cooking confidence and skills, and perceived high financial costs of healthy eating
[5,6]. We previously published a multilevel study to explore intrapersonal, social and environmental factors that might explain socioeconomic variations in women’s fruit and vegetable intakes
[2]. That study showed that lower intakes of fruits and vegetables amongst women of low SEP were not attributable to poorer access to stores in the local neighbourhood, but rather to intrapersonal factors, particularly less nutrition knowledge, and less consideration of health issues when purchasing foods. Other research has demonstrated that the use of strategies such as meal planning in advance and preparing a shopping list were associated with greater intakes of fruits and vegetables, suggesting that behavioural strategies may be important targets for healthy eating interventions
[7]. In the global context of rising food prices, strategies focused on effective food budgeting on a restricted income may also be particularly important in supporting persons experiencing socioeconomic disadvantage to eat more healthfully.

There remains little evidence from intervention studies about the most effective means of promoting healthy eating behaviours in persons of low SEP. Three literature reviews have suggested that behavioural interventions show promise in promoting increased fruit and vegetable consumption in the general population
[8-10]. Elements of effective behaviour change interventions identified in those reviews include goal-setting; recipe provision; and print materials. However, the reviews also identified a number of key gaps in the evidence. Firstly, evidence for the effectiveness of these strategies for promoting increased fruit and vegetable consumption amongst low-income or minority groups was very limited. For example, Ammerman et al. noted that ‘a serious deficit still exists in good quality published research designed to determine the relative efficacy of different intervention approaches in these high risk populations for whom conventional intervention approaches may be a poor fit with their needs’
[8]. Secondly, intervention evidence was limited by a heavy reliance on self-report measures to evaluate intervention effects. Thirdly, the reviews highlighted the lack of data on the cost-effectiveness of dietary interventions for promoting fruit and vegetable consumption. In the context of increasingly limited resources for public health, it is critical to establish whether interventions represent good ‘value-for-money’. Finally, few studies cited in the reviews reported on the mediators or mechanisms underlying any increases in fruit and vegetable consumption resulting from interventions. An understanding of these mediators is important for highlighting the most successful intervention elements and how they operate to change behaviour.

In summary, there is a need to develop and evaluate healthy eating interventions specifically addressing the needs and barriers faced by socioeconomically disadvantaged individuals; to evaluate these using objective measures; to report on intervention cost-effectiveness; and to identify the mediators of intervention effects. This paper reports on the protocol and methods of the ShopSmart 4 Health study, a randomised controlled trial designed to test the effectiveness and cost-effectiveness of a skill-building intervention promoting fruit and vegetable purchasing and consumption amongst socioeconomically disadvantaged women. Secondary aims were to test the impact of the intervention on self-efficacy for, perceived barriers to, and perceived affordability of, consuming fruits and vegetables; and to examine the contribution of self-efficacy, perceived barriers and perceived affordability as mediators of change in fruit and vegetable purchasing and consumption behaviours resulting from the intervention.

## Methods

### Study design, target group and setting

The ShopSmart 4 Health (referred to henceforth as ShopSmart) study is a randomised controlled trial with a 6-month intervention and pre-, post- and 6-month follow-up assessments of intervention effects, as outlined in Figure 
1. The Deakin University Faculty of Health Human Ethics Advisory Group approved the study (HEAG-H 188/09), and it was funded by the Australian Research Council Linkage Scheme (LP0990129). The trial is registered with the International Standard Randomised Controlled Trial Number Register (ISRCTN48771770). ShopSmart focuses on women of low SEP who shop at Coles supermarkets in socioeconomically disadvantaged suburbs of Melbourne, Australia. Melbourne is the capital of the state of Victoria, and with a population of approximately 4 million people in the greater geographical area, is the second-most populous city in Australia
[11]. Coles Supermarkets are the second largest grocery chain in Australia, with around 740 stores nationally. Women were the focus, since they are most often responsible for food purchasing and preparation, particularly in family households
[12,13]; they thus often influence the amount and type of food eaten by other family members. A large proportion of groceries are purchased in supermarkets. For example, Australians spend over $80 billion on supermarket and grocery shopping, which accounts for 62% of the retail food sector
[14]. However, there are very few supermarket-based eating interventions reported internationally, suggesting a potentially valuable missed opportunity to promote healthy eating. This study contributes to addressing this gap, building on a partnership with Coles supermarkets and the National Heart Foundation of Australia.

**Figure 1 F1:**
[figure not shown]
Flow chart showing participant recruitment, randomisation and evaluation of the ShopSmart intervention.

### Recruitment source

Participants were recruited from two catchment areas selected randomly from all neighbourhoods that were within 25km of Deakin University in Melbourne, Australia; were socioeconomically disadvantaged (i.e. being in the lowest quartile of disadvantage according to the Australian Bureau of Statistics Socioeconomic Index for Areas
[15]; and that had a Coles supermarket within the neighbourhood.

### Participant identification and recruitment procedure

Coles Supermarkets have a store loyalty program called FlyBuys, which is Australia’s largest shopping rewards program, with more than 10 million cardholders nationally, and more than 60% of Australian households being members (https://www.flybuys.com.au/export/sites/default/flybuys/content/information/mediacentre/FlyBuysFastFacts.pdf, retrieved 18 November 2012). Shoppers who sign up to FlyBuys are given a credit card style membership card which can be scanned every time a purchase above five Australian dollars is made at a participating FlyBuys business. This allows members to collect points which can then be exchanged for rewards. For this study, a sample of FlyBuys members who were women, aged 18–60 years and shopped at least once every two weeks in any Coles store in either one of the catchment areas was extracted using unidentified sales data from Coles and FlyBuys. A recruitment brochure was then mailed out to the women identified, explaining the study and asking them, if interested, to complete the eligibility questions and return the brochure to the researchers. In addition, a media promotion advertising the study was undertaken in the study neighbourhoods to coincide with the mailout, and attract additional interest. Respondents to either the mailout or media promotion who met all the following criteria were eligible and were subsequently enrolled into the study: woman, aged between 18 and 60 years; the main household shopper; shops regularly (at least once every two weeks) at Coles supermarkets in one of the two defined catchment areas; a FlyBuys (Coles store loyalty card) member, or willing to sign up to FlyBuys, and willing to use their FlyBuys customer loyalty card at Coles supermarkets for the next 12 months; willing to complete three surveys across the study period, and to have purchase data collected and analysed; the only woman in the household taking part in the study; able to speak, read and write in English, and to provide informed consent; and meeting income criteria. The income criteria were carefully selected in order to recruit the target sample of socioeconomically disadvantaged women, without the need for asking potential participants sensitive income questions upon initial registration of interest. For this purpose, women were simply asked if they met ANY of the following criteria (they were not required to specify which): had a household income below AUS$1000 per week after tax; or were the holder of a health care card (a Government card available to low-income earners or welfare beneficiaries); or their main income was derived from a pension or welfare benefit. The household income cutpoint was chosen to correspond to slightly under the median after- tax household income (ignoring household composition); reported as $1183/week in August 2010 (ABS, see http://www.ausstats.abs.gov.au/ausstats/subscriber.nsf/0/DBE855896D8CA36DCA2578FB0018533C/$File/65230_2009-10.pdf). Participants gave their informed consent and all participants, whether intervention or control group, were provided with compensation to the total value of approximately $80 ($20 for each survey completed; 1000 FlyBuys bonus points, worth approximately $15; and small gifts such as pens and water bottles) for their time and commitment to the study.

### Intervention

The intervention was guided by the social cognitive theoretical model
[16], which proposes that individuals adopt new behaviours through social learning, either through imitation of others, or through media sources. In addition, the intervention draws on empirical evidence of the key determinants of eating behaviours in socioeconomically disadvantaged groups, including past work suggesting the importance of addressing nutrition knowledge, budgeting and food planning and preparation skills, and perceived cost barriers
[2,5-7].

An intervention mapping approach was undertaken
[17] to ensure that the intervention was underpinned by a strong theoretical, empirical, and practical foundation. A literature search was conducted to identify existing materials that target increasing fruit and vegetable consumption in socioeconomically disadvantaged groups, and that addressed the key determinants and constructs of social cognitive theory. New materials were developed where there was insufficient or inadequate existing content to address the study aims. The findings of the search and mapping process suggested that selected printed materials, in conjunction with a face-to-face component, both focused on building skills, on budgeting and value for money, were promising strategies. A set of eight educational and skill-building newsletter and behaviour change resource packages, as well as a supermarket tour to complement and provide practical demonstrations of the printed information, were then developed by Accredited Practising Dietitians in collaboration with study investigators. The approach and materials shared some similarities to those adopted in a sister study, SHELf, conducted by the investigators
[18]; however, ShopSmart was specifically targeted to addressing the needs of women of low SEP, and hence materials were targeted accordingly, as follows.

The materials targeted the proposed theoretical mediators, nutrition self-efficacy, perceived affordability and other perceived barriers to fruit and vegetable consumption. Intervention elements included improving nutrition knowledge and confidence, including increasing awareness of the importance of fruit and vegetables to health, highlighting the range of low-cost fruits and vegetables available and their uses, and the relative costs compared with other foods and in-season produce. The value of more affordable options (such as frozen or tinned fruits/vegetables) was also a strong focus. Women were encouraged to set specific goals in order to increase their own and their families’ vegetable consumption to meet the guidelines of 5 serves per day
[19]. They were provided with goal-setting exercises to record these goals, and were reminded in each resource package to revisit them, and provided with feedback/suggestions for progressing. Skill-building activities were designed to foster behavioural skills in budgeting; meal planning; label reading and food selection in the supermarket; meal preparation strategies including preparing shopping lists prior to getting to the supermarket; and food safety and long-term storage. The packs also included advice on overcoming commonly-reported barriers to increasing fruit and vegetable consumption, such as replacing more expensive fresh produce with frozen/tinned; and involving children in choosing/shopping for/preparing meals.

### Skill-building resource packs

The eight editions of the printed newsletters and resource packs were distributed to intervention participants, with a pack sent every two weeks for the first two months and monthly for the remaining four months of the intervention. The emphasis of these newsletters was on budgeting, goal setting; meal planning; cutting costs; taste and increasing confidence and family involvement in fruit and vegetable preparation and consumption. One key source of newsletter content was FoodCent$
[20], an innovative intervention approach aimed primarily at increasing food budgeting skills to support people with limited budgets to allocate money to healthier foods. While the FoodCent$ trial showed positive changes in cooking, shopping and eating behaviours, it had not been evaluated in a randomised controlled trial. In the present study, newsletters incorporated elements of FoodCent$, including resources for participants to develop budgeting and food shopping skills.

Each newsletter also included two recipes for healthy, inexpensive meals incorporating fruits and vegetables, with cost and nutritional information provided. Resource packs also included supplementary skill-building materials (goal-setting activities, menu planners, shopping lists, seasonality and food preparation and storage guides, self-monitoring exercises) as well as links to useful websites. There was a strong focus in all resources on the specific needs of women of low SEP, particularly affordability and nutrition-related skills. The packs were reviewed by experts in the field before being pilot tested in a convenience sample of 34 women. Following pilot-testing, minor revisions were made to improve readability, interest, tone and layout.

### Supermarket tours

Supermarket tour content was developed by Accredited Practising Dietitians, and focused on reinforcing the materials provided in resource packs, as well as on providing practical, hands-on skills for food selection and preparation. Topics included health benefits; seasonality and selection of fruit and vegetables; tinned/frozen fruit and vegetable options; label reading; appropriate portion sizes; cost saving; and practical strategies for increasing fruit and vegetables in everyday meals. The emphasis was on affordability, convenience/time-saving, taste and increasing confidence/ self-efficacy. Each supermarket tour ran for approximately one hour, and was conducted by one Accredited Practising Dietitian assisted by one other member of the research staff. The tours were attended by small groups (n=1-6) of participants and held in Coles supermarkets in the study areas at times convenient to participants.

### Control group

Participants in the control group completed the assessments only, until the intervention and 6-month follow-up were complete, at which point they were offered all printed intervention materials in a single pack.

### Measures

Outcome data were collected from both intervention and control participants pre- and immediately post intervention and at 6 months following the completion of the intervention. Economic data were collected alongside the outcome data from Coles electronic sales data and participants’ self-reported postal questionnaires. Additional data on the resources used to provide the intervention were collected from records kept by project staff. Process evaluation data were collected from intervention participants immediately post-intervention and also after the supermarket tour for those completing this activity.

### Outcome variables

The primary outcome variables are vegetable purchasing and consumption. Measures of food purchasing were obtained using electronic sales data provided by Coles for consenting participants via their Flybuys cards, which participants were asked to scan each time they shopped at Coles. Individualized electronic purchasing data for each participant were collected for a 3-month period prior to intervention (retrospectively following consent), and continually during the 6-month intervention and the 6-month follow-up. Participants’ purchasing data, identified by their unique Flybuys card number, were provided in tab-delimited files and uploaded to a SQL database. The files included a unique product code; product descriptor; amount/quantity purchased; and the related expenses. For each participant, all fresh, frozen, dried and tinned vegetable items purchased were identified by product codes and the quantities (by weight) and the total expenses per each item ($).

All other primary and secondary outcomes were assessed by self-report surveys. Vegetable consumption was assessed via two measures. Firstly, respondents were asked ‘About how many serves of vegetables do you usually eat per day? (1 serve = ½ cup cooked vegetables or 1 cup salad vegetables)’ Eight response options ranged from I don’t eat vegetables, to 6 or more serves per day. This item was adapted from the 1995 National Nutrition Survey
[21], where it was shown to adequately discriminate between groups with different vegetable intakes assessed by 24-hour recall. Secondly, respondents were administered a Food Frequency Questionnaire
[21], including 21 items assessing the average consumption of commonly-consumed vegetables in the past 6 months, with nine response options ranging from never or less than once/month, to 6 or more times per day.

Secondary outcomes are fruit purchasing and consumption, assessed in the same way as vegetable purchasing/consumption. Frequency of consumption of energy-dense, nutrient poor foods and beverages were measured by the survey as a marker of unintended consequences (for example, increases in intakes of confectionery or sugar-sweetened beverages). Food security was assessed as a potential consequence of the intervention (‘In the last 12 months, were there any times that you ran out of food, and couldn’t afford to buy more?’)
[21]. The survey also assessed theoretical mediators and behaviours and attitudes targeted by the intervention to promote these: self-efficacy for increasing fruit and vegetable consumption; perceived affordability of, and barriers to, fruit and vegetable consumption; cooking confidence; behavioural strategies related to food planning/shopping; and considerations when grocery shopping. Finally, the following sociodemographic characteristics were assessed: age, country of birth, relationships status, highest qualification (own & partner’s if applicable), employment status (own & partner’s), income category (own & household) and number of dependents; and number of adults and children for whom groceries were bought. Other covariates assessed by survey included height/weight, dieting for weight control, vegetarianism, and pregnancy.

### Economic evaluation

A cost-consequences analysis comparing the incremental costs and outcomes of the skill-building intervention to the control group will be conducted under a broad societal perspective. Key costs for the economic evaluation include program costs (dietitian and other researcher time in relation to the intervention, intervention material costs and travel expenses) and family costs (family time spent on the intervention and related travel costs, plus expenditure on fruit and vegetable consumption). The possible future effects of this nutrition education program and the related costs such as the reduced healthcare costs, the improved quality of life and the increased workforce participation are beyond the extent of the economic evaluation of this study and therefore will not be considered in the economic analysis. All costs and outcomes are expressed in their natural units. Participants will be asked where and how often they do grocery or food shopping, the amount of fruit and vegetables are bought from Coles, the average time spent food shopping at Coles and the mode of transportation as well as the travel time to get to Coles stores from home. Measured resource use will be valued using the cost of each unit of resource use such as Coles electronics sales data for household expenditure on fruit and vegetables, Australian Bureau of Statistics estimates of average Australian earnings for family time costs, Royal Automobile Club of Victoria (RACV) estimates of travel costs, etc. Extensive sensitivity analyses will be conducted on key costs and outcomes. No discount factor is applied for costs and outcomes in this less than one year trial.

Process evaluation will focus on intervention participants’ experience of all aspects of intervention implementation.

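### The family food cost counts only fruit and vegetable spending, so produce paid for by cutting other groceries overstates the incremental family cost

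*Protocol article*

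**What the plan says.** The protocol article plans a cost-consequences analysis of intervention against control, which "will be conducted under a broad societal perspective" (Economic evaluation). Family costs are given as "family costs (family time spent on the intervention and related travel costs, plus expenditure on fruit and vegetable consumption". The food element is valued from "Coles electronics sales data for household expenditure on fruit and vegetables". The section openly excludes one group of items (later health care savings, quality of life and workforce effects) but says nothing about spending on other groceries.

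On mechanism, Skill-building resource packs names a budgeting programme as a key source of newsletter content, "aimed primarily at increasing food budgeting skills to support people with limited budgets to allocate money to healthier foods". The Intervention section also describes advice on "replacing more expensive fresh produce with frozen/tinned".

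On data, Outcome variables says of the sales records: "The files included a unique product code; product descriptor; amount/quantity purchased; and the related expenses". Vegetable items were picked out by product code, and fruit is assessed in the same way. Purchases are available for 3 months before the intervention, through its 6 months, and through 6 months of follow-up.

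**The concern.** Part of the intervention's purpose is to help households on tight budgets spend differently. A family that buys more vegetables by buying less of something else has changed the make-up of its basket, not necessarily its total. From a societal or family viewpoint the incremental food cost is the change in the whole food bill. If only the produce line is counted, the rise is recorded and the matching fall is not.

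At stake is the family-cost line of the economic results. A reader who adds programme, time, travel and food costs to judge value for money would be adding a food item that is too large whenever produce displaced other purchases. The effectiveness analysis is not affected.

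**Working it through.** The article states no food cost, so there is no figure of the plan's to reproduce. The check is an accounting identity followed by illustrations whose prices and amounts are assumptions.

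**Identity.** All terms are between-arm differences per household.
- F = increase in fruit and vegetable spending.
- G = reduction in other grocery spending.
- Cost counted by the plan = F.
- Net food cost = F − G.
- Overstatement = F − (F − G) = G.

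If a fraction d of the extra produce spending is financed from other groceries, then G = d × F and the net cost is F × (1 − d). If other grocery spending rose instead, G would be negative and the error would reverse.

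**Illustration 1: an assumed AUD 5 per week moved to produce.** Two horizons are shown. The intervention lasts 6 months and purchases are followed for a further 6, while Economic evaluation calls this a trial of under one year.
- 26 weeks: F = 5 × 26 = AUD 130.
- 52 weeks: F = 5 × 52 = AUD 260.

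| Fraction displaced (d) | Overstatement, 26 weeks | Overstatement, 52 weeks |
|---|---|---|
| 0 | AUD 0 | AUD 0 |
| 0.5 | AUD 65 | AUD 130 |
| 1 | AUD 130 | AUD 260 |

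**Illustration 2: scaled to the trial's own target.** Sample size and justification gives a target of 0.5 serves per day and a vegetable serve of 75 g. The price of AUD 2 to 6 per kg and a household of three who all change equally are assumptions.
- 0.5 × 75 g = 37.5 g per day, or 6.83 kg per person over 182 days and 13.69 kg over 365 days.
- One person: AUD 14 to 41 over 182 days; AUD 27 to 82 over 365 days.
- Household of three: AUD 41 to 123 over 182 days; AUD 82 to 246 over 365 days.

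With full displacement each of these amounts is entirely overstatement; with half displacement, half of it is. The AUD 5 per week used above lies just over the top of the household range, so it is on the high side for vegetables alone.

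**How the counted cost moves with the effect.** At an assumed constant AUD 4 per kg, one person over 365 days, effects of 0, 0.25, 0.5 and 1.0 serves per day give counted costs of AUD 0, 27, 55 and 110. With full displacement the net cost is 0 in each case.

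**Limit of that pattern.** The same section gives a mean intake of 1.9 serves. A rise to 2.4 serves leaves vegetable spending unchanged if the price per serve falls by 1 − 1.9/2.4 = 20.8%. A move to cheaper forms of produce could do this, and then there is no extra produce outlay to be financed from other foods.

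**The case against.** The strongest reply is that the cost list is open. It is introduced as covering key items, the valuation sources end with an et cetera, wide-ranging sensitivity analyses of the main costs and outcomes are promised, and a journal article leaves costing detail to a fuller document. This is fair, but it does not supply the offset. Within family costs the only food item named is produce, the only price source named for it is produce sales, and no sensitivity analysis is described that would bring in other groceries.

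Several stronger readings are tempting, and the documents do not support them:
- **The food budget is fixed.** The text speaks of limited budgets, and does so when describing the source programme. It does not say that total spending is constant, so full displacement is the upper end of a range and not the expected case.
- **The intervention must look costlier the better it works.** This holds only if price per serve is steady. The advice on frozen and tinned produce works the other way.
- **Vegetable purchasing is double-counted as cost and benefit.** A cost-consequences analysis lists costs and outcomes separately in natural units. There is no ratio or net sum in which one quantity could enter twice, and the purchasing measure distinguishes weight from dollars.
- **Store switching is ignored.** The survey asks where women shop and how much of their produce comes from Coles, so the information is collected. What is unstated is how it will be used. Total Coles spend would also be exposed to switching.
- **The cost-effectiveness aim is contradicted.** The Background does say the trial is "designed to test the effectiveness and cost-effectiveness of a skill-building intervention", but the abstract discloses the cost-consequences approach and incremental costs and outcomes are to be reported. This is a matter of labelling, not an error.

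**Conclusion.** The point holds in a limited form. Followed as written, the plan overstates incremental family cost by whatever amount of other grocery spending is displaced. The intervention is partly designed to bring about such displacement, so the possibility is a real one. Whether it happens, and how much, cannot be known from the documents.

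Under the assumed AUD 5 per week, the overstatement is between AUD 0 and AUD 130 per household over the intervention, and at most AUD 260 over 52 weeks. These figures show scale only; they rest on an assumed weekly amount and an unknown displaced fraction. The distortion sits in one line of a disaggregated cost table and does not touch the primary effectiveness analysis.

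**What to change.** In Economic evaluation, define the net family food cost as the between-arm difference in total food or grocery spend from the same Coles files. Adjust it for the 3-month pre-intervention spend, and leave out non-food items where product codes allow. Show it beside fruit and vegetable spend, so that a reader sees both the produce outlay and how far it was offset. State the horizon for both. Add a named sensitivity analysis for store switching that uses the survey answers on where women shop and how much produce they buy at Coles.

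The cost is extra analysis, probably with no new collection: picking out vegetables by product code implies that the files hold other items too, which should be confirmed. Total spend is noisier than produce spend, so its interval will be wider, and it still misses purchases at other shops. For both reasons it should accompany the produce figure and not replace it in the table.
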